### Study population

Pregnant women booking in to give birth at one of two sites during the recruitment period will be invited to participate in the study and will be randomly allocated to caseload midwifery care versus routine care according to a post-consent method using accepted concealment measures endorsed by the NHMRC. The two sites are - large tertiary maternity hospitals in Sydney (site 1) and Brisbane (site 2).

### Study Power

With 750 women or more in each of the intervention and control arms the study is powered (based on 80% power; alpha 0.05) to detect a difference in caesarean section rates of 29.4 to 22.9%; instrumental birth rates from 11.0% to 6.8%; and rates of admission to neonatal intensive care of all neonates from 9.9% to 5.8% (requires 721 in each arm). The study is not powered to detect infant or maternal mortality, however all deaths will be reported. Secondary outcomes will include rates of smoking cessation (eg 14.8% to 9.9% needing 747 women in each arm) and breastfeeding initiation and duration. We have calculated a sample to include a 30% attrition rate; therefore we aim to recruit a total of 1,950 women. All outcome measures identified by the Cochrane Protocol [19] will be collected. Individual hospital data bases and a purposefully designed data base will collect all primary and secondary outcome and process measures in addition to most cost outcome measures.

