#### Trial Eligibility

Women will be eligible for trial entry if they are less than 24 completed weeks of pregnancy and a minimum of 18 years old at booking in. At the participating centres research midwives will recruit the required number of women in the experimental arm over 24 months. We will enroll 1950 women in anticipation of no more than a 30% attrition rate.

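### The 1,950 recruitment target adds 30% to 1,500 instead of dividing by 0.70, so at the stated 30% attrition about 682 women per arm remain, fewer than the plan says it needs

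*Protocol article*

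**What the plan says.** The Study Power section sets the requirement: "With 750 women or more in each of the intervention and control arms the study is powered" ("based on 80% power; alpha 0.05"). The differences to be detected are caesarean section 29.4% against 22.9%, instrumental birth 11.0% against 6.8%, and admission to neonatal intensive care 9.9% against 5.8%. It gives 721 per arm for neonatal admission. As a secondary example it gives smoking, 14.8% against 9.9%, with 747 per arm.

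The same section then sets the recruitment target: "We have calculated a sample to include a 30% attrition rate; therefore we aim to recruit a total of 1,950 women". The Trial Eligibility section repeats it: "We will enroll 1950 women in anticipation of no more than a 30% attrition rate". No other derivation of 1,950 is given.

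**The concern.** An attrition allowance should ensure that the required number remains after the stated loss. If a fraction *a* of those enrolled is lost, the enrolment needed is the required number divided by (1 − *a*). Multiplying by (1 + *a*) gives too few, and the gap widens as *a* grows. At 30% it is no longer a matter of rounding.

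The target of 1,950 is exactly what multiplication gives. The plan's three statements, 750 per arm for analysis, 1,950 enrolled and 30% attrition allowed for, therefore cannot all be true. A reader or funder would conclude that the trial can lose 30% of its women and keep its stated power, and on the document's own figures that is not so. The monitoring of follow-up is affected too: attrition between 23% and 30% would look acceptable although the required number had already been lost.

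**Working it through.** **Inputs** (Study Power, unless noted): 750 per arm, 1,500 in total; 80% power; alpha 0.05; the four pairs of rates above; 30% attrition; target 1,950. Trial Eligibility expresses the 30% as a loss from the 1,950 enrolled. Two assumptions are mine: equal arms and a two-sided test. The document does not state sidedness, but two-sided calculations come close to its figures.

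**Step 1. Reproduce the target.**
- 1,500 × (1 + 0.30) = 1,950, an exact match.
- 1,500 / (1 − 0.30) = 2,142.9, so 2,143, which does not match.

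**Step 2. Apply the stated attrition.**
- 1,950 × 0.70 = 1,365, or 682.5 per arm.
- Shortfall against 1,500: 135 women, or 9% (135/1,500).
- Largest attrition that keeps 1,500: 1 − 1,500/1,950 = 23.1%.

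This step needs no power formula: 682 is below 750, 747 and 721.

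**Step 3. Find the method behind the per-arm figures.** With d = p1 − p2 and p̄ the mean of the two rates:

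n = [1.96 √(2p̄(1 − p̄)) + 0.842 √(p1(1 − p1) + p2(1 − p2))]² / d²

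The continuity-corrected version is n_c = (n/4) [1 + √(1 + 4/(n d))]². Results are rounded up.

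| Outcome | Uncorrected n per arm | Corrected n per arm | Stated |
|---|---|---|---|
| Caesarean | 717 | 747 | 750 (common figure) |
| Instrumental birth | 721 | 768 | 750 (common figure) |
| Neonatal admission | 675 | 723 | 721 |
| Smoking | 707 | 747 | 747 |

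The corrected formula matches smoking and comes within 2 of neonatal admission. It does not fit instrumental birth, where it asks for about 767 (767.2 before rounding up), more than the stated 750.

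**Step 4. Power at 682.5 per arm.** Let s0 = √(2p̄(1 − p̄)/n) and s1 = √([p1(1 − p1) + p2(1 − p2)]/n). Power is Φ[(d − 1.96 s0)/s1], and with the correction d is replaced by d − 1/n.

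For caesarean section, p̄ = 0.2615, s0 = 0.02379 and s1 = 0.02372.
- Uncorrected: (0.065 − 0.04663)/0.02372 = 0.774, power 78.1%.
- Corrected: (0.065 − 0.00147 − 0.04663)/0.02372 = 0.713, power 76.2%.

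| Outcome | 682.5 per arm, corrected | 682.5 per arm, uncorrected | 750 per arm, corrected | 750 per arm, uncorrected |
|---|---|---|---|---|
| Caesarean | 76.2% | 78.1% | 80.2% | 81.8% |
| Instrumental birth | 74.9% | 77.8% | 79.0% | 81.6% |
| Neonatal admission | 77.6% | 80.5% | 81.6% | 84.0% |
| Smoking | 76.1% | 78.6% | 80.2% | 82.3% |

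An exact binomial calculation for the uncorrected chi-squared test at 682 per arm agrees: 78.1%, 78.1%, 81.0% and 78.8%, in the same order.

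**The case against.** **The 30% could be a margin added to 1,500.** The Study Power sentence taken alone might allow that reading. The Trial Eligibility sentence does not, because it sets the 30% against the 1,950 enrolled.

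**The stated power is not lost throughout.** A reader might infer that every listed outcome falls below 80%. The document does not support this as a flat statement. It holds only with a continuity correction that the document never names, and the Analysis section speaks simply of chi-squared tests. Without the correction, neonatal admission keeps about 80% and the other outcomes lose about 1.5 to 2 points against 80%. With it, instrumental birth is already at 79.0% at 750 per arm, so its fall to 75% is not wholly due to the attrition step. This objection stands, and both sets of figures should be shown.

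**Birth outcomes may suffer little loss.** Study Power says that hospital databases and a purpose-built database will hold the primary and secondary outcomes, and the Analysis section includes withdrawals and losses under intention to treat. With no loss at all (975 per arm), the same formulas give 89–92% power. This limits the likely consequence. It does not remove the contradiction, because Study Power attaches the 30% to this calculation without exempting birth outcomes, and intention to treat does not supply outcomes that were never recorded.

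A reader might go further and infer that the 30% is mainly survey non-response. No section says so. The recruitment sections describe women randomised on verbal consent who leave the trial if they then decline written consent or prove ineligible, and Outcome measures lists miscarriages. Either could reduce the numbers for birth outcomes too.

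**Conclusion.** The sample-size statement is wrong as written. A target of 1,950 does not allow for 30% attrition while leaving 750 per arm. It leaves about 682, and it protects 750 only up to 23.1% attrition. This conclusion rests on the document's own figures and on equal allocation.

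The effect on power is real but modest. If the full 30% is lost, power is about 75–78% with the continuity-corrected formula, which approximately reproduces 721 and 747, and about 78–80% with an uncorrected chi-squared test. These ranges assume two-sided testing. How far birth outcomes would be affected cannot be settled, because the document does not say which losses the 30% covers.

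**What to change.** Keep 1,950 and amend Study Power and Trial Eligibility together, with one of two statements:

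- 1,950 women allow for up to 23% attrition while retaining 750 per arm; or
- 30% attrition would leave about 682 per arm, with power for the listed differences of about 75–78% (continuity-corrected) or 78–80% (uncorrected chi-squared).

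In the second case, name the method, since the answer for neonatal admission depends on it. In either case, state which outcomes the 30% applies to, and do not describe it as survey loss unless the sponsor can confirm that.

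The cost is a few reworded sentences and a slightly less favourable attrition or power figure, with no extra women. For comparison, keeping both 750 per arm and 30% attrition would take 1,500/0.70 = 2,143 women, which is 193 more than planned.

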#### Definitions of Control and Intervention

The lead professional for the continuum of the antenatal, intrapartum and postnatal periods will be the criterion for the classification of care as caseload midwifery or routine (medical doctor-led) care [19].

***CONTROL **Standard or Routine care*: the designated obstetrician is the lead professional. Women are booked under the hospital consultant on call for the day of booking, and the responsibility for the delivery of care, from initial booking through the postnatal period, rests with the public maternity hospital service. Women allocated to the control group can choose from the standard hospital options for care which include midwives clinic antenatally; GP shared care antenatally; followed by general public hospital care in labour and in the postnatal ward. This may involve women seeing a different midwife for every visit; care by junior medical obstetric staff; or shared care with an accredited general medical practitioner (GP) (i.e. the GP provides the woman's antenatal care, usually nearer to her home, but the woman is booked for extra antenatal care, labour, birth and postnatal care at the hospital). Women may see an obstetrician during pregnancy with other referrals or consultation as necessary. When women come into the hospital for labour, birth and postnatal care they will be cared for by whichever midwives and doctors are rostered for duty. For women in the control and intervention arms at each site the care will be provided according to the same hospital guidelines and protocols of each site.

***INTERVENTION **Caseload Midwifery care: *Women allocated to the caseload intervention will receive antenatal, intrapartum and postpartum care from a named caseload midwife who will be backed up when necessary by other caseload midwives from within her Midwifery Group Practice. Each named caseload midwife works in a Midwifery Group Practice of four full time equivalent midwives each working a cycle of 152 hours during each four week period. Caseload midwives must be independent of the hospital rosters and employed on an annual salary to allow for workload to be self managed within each Midwifery Group Practice and responding to the needs of the women in their caseload. The named midwife is on call for the woman's labour and birth except in designated circumstances such as annual leave; sick leave; having more than one woman in labour; or if it is on one of the two days per week that the named midwife is scheduled to not work or be on call. Care will then be provided by a back-up caseload midwife from the Midwifery Group Practice. The caseload midwife is the woman's lead professional but one or more consultations with medical doctors may be part of routine practice [24]. Midwifery care is offered simultaneously with medical care if required. In addition to providing care until after the birth of the baby, the named caseload midwife (or a back up midwife from the Midwifery Group Practice) will attend the hospital on most days to provide some postnatal care until discharge and will provide full domiciliary care following discharge from hospital. Care will be provided according to hospital guidelines and protocols for up to six weeks following birth.

#### Trial Eligibility

Women will be eligible for trial entry if they are less than 24 completed weeks of pregnancy and a minimum of 18 years old at booking in. At the participating centres research midwives will recruit the required number of women in the experimental arm over 24 months. We will enroll 1950 women in anticipation of no more than a 30% attrition rate.

#### Exclusions

Women will be excluded from the trial if they are electively booked to give birth via caesarean section at the time of booking in; or are already booked with a named care provider (Obstetrician/GP/midwife).

#### Trial Recruitment

At site [1] women will be recruited using three strategies depending on point of first contact.

**1**. When the woman contacts the hospital by phone for booking, the administration desk will send out information leaflets informing women of (a) the opportunity to book with a caseload midwife as part the care offered at the hospital and (b) inviting them to participate in the study before the first visit to the hospital antenatal clinics. Women will attend the hospital antenatal clinic for their booking visit. At the first visit (booking clinic) women will be seen by a research midwife who ascertains if the woman has previously received written information and if so, she will be invited to participate. Following written consent, the midwife will randomise the woman to the intervention caseload midwifery care with a named midwife or routine care via a central telephone randomisation service (NH&MRC method); and enter details on the Trial Register and Daily Log Book. (The NHMRC administered telephone randomisation method guarantees both random sequence generation and allocation concealment according to CONSORT guidelines).

**2**. When a booking referral from the woman's General Practitioner is sent to the hospital, the administration desk contacts the woman and informs the woman of (a) the opportunity to book with a caseload midwife as part the care offered at the hospital, and (b) if eligible invite them to participate in the study before the first booking visit. Interested women will be sent information leaflets. The woman is contacted by phone by the research midwife to ensure the information has been received, assess the woman's understanding of the study, answer any questions, and obtain verbal consent to participate and be randomised. Once verbal consent is obtained the trial procedure is the same as that above and her details are entered onto the Trial Register and Daily Log Book. Consent is formalised in writing at the first booking visit. At this stage, if the woman declines to give written consent or is ineligible, she is not enrolled in the trial. Women not wishing to participate in the study will progress through the antenatal clinic as usual.

**3**. When the woman has not received written information, at the booking clinic, she will be seen by a research midwife, who will provide her with written information and an opportunity to discuss the study. Before being invited to participate in the study, the woman will be given the opportunity to defer her decision to participate until the next antenatal appointment where she will be seen again by the antenatal clinic midwives and the research midwife. If the woman wishes to decline or accept the invitation to participate at this first visit, she may do so. She may contact the research midwives at a later time to participate in the study. Once women have given written consent to be involved in the trial, the trial procedure is the same as that above. Details of these women will also be recorded in the Trial Register and Daily Log Book Women not wishing to participate in the study will progress through the antenatal clinic as usual.

**At Site 2 **pregnant women will be randomly allocated to caseload midwifery care or routine care during pregnancy.

1. On receipt of referral from the general practitioner, the GP Liaison will identify women eligible for caseload care. This process is guided by availability of places on caseload group practice models of care in association with the locality of the home address of women who book.

2. Women who qualify on these grounds will be telephoned to be informed of their acceptance to book at Site 2 and the availability of caseload midwifery care in their area. They will have the models of care briefly outlined, and be invited to participate in the trial.

3. Interested women will receive a brochure on models of care, and a M@NGO trial brochure in the post.

4. One week following postage, the research midwife will provide a follow up phone call to ensure the information was received, assess the woman's understanding of the study, answer any questions, and obtain verbal consent to participate and be randomised. We do not expect that this will create unnecessary delays as at present women may wait several weeks before they receive a letter confirming their acceptance to Site 2, with the models of care brochure and a booking appointment.

5. Once verbal consent is obtained and documented, the research midwife will randomise the woman to caseload or routine care via a central telephone randomisation service (NH&MRC method); and enter details onto the Trial Register and Daily Log Book

6. At the first booking visit women who were telephone randomised to take part in the study will confirm and formalise participation in the trial by giving written consent at the first booking visit in the home.

7. In the standard care model written consent will be obtained at the first booking visit in the hospital or community-based antenatal clinic.

8. At this stage, if the woman declines to given written consent or is ineligible (meets exclusion criteria) she is excluded from trial, and her care will be 'as usual' i.e. standard care.

Once women have given written consent to be involved in the trial, the trial procedure is the same as Site 1 above. Women not wishing to participate in the study will progress through the hospital or community antenatal clinics as usual. Details of these women will also be recorded in the Trial Register and Daily Log Book.

### Differences between Site 1 and Site 2

Although there is a slight difference in the recruitment process for the trial at the two sites, the integrity of the randomisation process is safeguarded by the fact that there is equipoise in the decision process for women regarding which model of care they will receive. Women who have a stated preference for either model are not invited to be randomised to a model of care. The proposed recruitment method for Site 2 differs slightly from the process employed at site 1 on two counts:

i. At site 1 all women attend a first booking visit at the hospital antenatal clinic before they are allocated to a model of care, including caseload care. At Site 2 women are allocated to a model of care, including caseload care by the GP Liaison, *prior to *the first booking visit.

ii. At site 1 the first booking visit occurs in the antenatal clinic, which enables research midwives' to provide information about the trial and obtain written consent. At Site 2 women are offered information by telephone and the initial consent is received by telephone. All women allocated to MGP have a home booking visit and do not attend the antenatal clinic at all. It is not feasible for the research midwife to accompany MGP midwives to every home visit to give information about the trial and obtain written consent in the first instance. See above the process for Site 2 to further clarify.

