### Analysis

Analysis will be by intention to treat which will include withdrawals and losses to follow up. There should be minimal differences in the baseline characteristics between groups due to the randomisation process. Statistical adjustment may be needed if important differences arise in baseline characteristics. Relative risks with 95% confidence intervals for the primary outcomes will be calculated. Measures of categorical data will be analysed with chi-squared tests and continuous data will be analysed with t-tests. Logistic regression and multiple linear regressions will be used if necessary to adjust for confounding for binary and continuous outcomes.

Risk will be controlled for in the statistical analysis and identified at the onset of labour rather than at enrolment in the study. Women will be categorised dichotomously as 'at low risk' and 'not low risk' according to maternal risk status at the time of the onset of labour. The risk factors and levels of risk are well defined in the ACM Guidelines [24] as level B or C - however, all definitions of risk will be available in the publication of the study.

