### Group Allocation

The randomisation schedule will be prepared by a researcher not involved with treatment allocation. Following written informed consent from the woman, the research midwife will telephone the randomisation service. Details of the woman's consent and trial entry data will be recorded. The midwife will then be informed of the group (caseload midwifery or routine hospital care) to which the woman has been randomly allocated and the woman will be issued with a unique 4 digit study number. Study group allocation will be recorded on the Trial Register and Daily Log Book. To assess the comparability of the study groups, baseline demographic and medical information will be collected from the medical record at the time of entry into the study. Because the structure of practice is so different; there should be minimal opportunity for cross overs to occur. No attempt will be made to blind the identification of women randomised to either arm of the study.

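### At Site 2, women are randomised on verbal consent and can be excluded afterwards, at a booking visit that differs by arm; this conflicts with intention to treat and can bias the caesarean comparison

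*Protocol article*

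**What the plan says.** **Site 2 (Trial Recruitment, steps 5 to 8).** Step 5: "Once verbal consent is obtained and documented, the research midwife will randomise the woman to caseload or routine care". Steps 6 and 7 take written consent later, at the first booking visit: at home in step 6, and in a hospital or community clinic for standard care in step 7. Item ii of the section on differences between the sites confirms that all women allocated to a Midwifery Group Practice are booked at home and do not come to the clinic. Step 8: "At this stage, if the woman declines to given written consent or is ineligible (meets exclusion criteria) she is excluded from trial"; her care is then standard care.

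**Exclusions.** "Women will be excluded from the trial if they are electively booked to give birth via caesarean section at the time of booking in".

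**Group Allocation.** "Following written informed consent from the woman, the research midwife will telephone the randomisation service". The same section says that the midwife is then informed of the group and that allocation is not blinded.

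**Analysis.** "Analysis will be by intention to treat which will include withdrawals and losses to follow up". Justification for RCT adds that women are analysed in the group to which they were allocated, and that all exclusions will be reported.

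**Site 1, strategy 2 (GP referral).** Verbal consent to take part and be randomised is obtained by telephone, the procedure is then said to match strategy 1, and written consent follows at the booking visit: "At this stage, if the woman declines to give written consent or is ineligible, she is not enrolled in the trial".

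**The concern.** At Site 2 final entry to the trial is settled after allocation, at a visit whose setting already reveals the arm. Three features allow removal to differ by arm.

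- **Unequal incentive to sign.** A woman who declines receives standard care. A control woman who declines therefore gives up nothing, while a caseload woman who declines loses her caseload midwife.
- **An exclusion criterion tied to a primary outcome.** An elective caesarean booking is assessed as of booking in, which at Site 2 comes after randomisation.
- **No pre-randomisation check of the exclusion criteria is described at Site 2.** The screening in step 1 concerns available places and home locality.

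If removals differ by arm in number or in caesarean risk, the groups compared are no longer the groups randomised. Calling the analysis intention to treat does not restore them, and baseline adjustment cannot be relied on to do so.

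**Working it through.** **1. The passages side by side.**

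- Order of consent and randomisation: Group Allocation puts written consent first; Site 2 steps 5 to 7 put it second. Both cannot be followed.
- Who is analysed: Analysis and Justification for RCT keep women in their allocated group; Site 2 step 8 removes some randomised women from the trial. Reporting exclusions discloses those removals but does not put the women back in the analysis.
- Site 1, strategy 2: consent to be randomised is taken by telephone, yet the procedure it refers back to randomises after written consent, and item i of the section on site differences says that all Site 1 women attend the booking visit before allocation. The order is ambiguous.

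**2. The plan's own figure.** Study Power states that with 750 women or more per arm "the study is powered (based on 80% power; alpha 0.05") "to detect a difference in caesarean section rates of 29.4 to 22.9"%. Sidedness is not stated; I assume two-sided. With mean proportion 0.2615 and difference 0.065:

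n = [1.96·√(2·0.2615·0.7385) + 0.8416·√(0.294·0.706 + 0.229·0.771)]² / 0.065² = 717 per arm.

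The continuity correction, (n/4)·[1 + √(1 + 4/(n·0.065))]², gives 747. The stated 750 is reproduced, so this point does not rest on a sample-size error.

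**3. Bias from unequal removal, with no true effect.** Let p = 0.294 be the caesarean rate in both arms, e the excess share removed from one arm, and q the caesarean rate among those removed. The documents give neither e nor q; both are assumed ranges.

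- Rate among those kept: r = (p − e·q)/(1 − e)
- False difference: d = p − r = e·(q − p)/(1 − e)
- False-positive rate: 1 − Φ(1.96 − d/SE) + Φ(−1.96 − d/SE), with SE = √[p(1−p)/n + r(1−r)/(n(1−e))]

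Here n = 750, or 975 (half of the 1,950 to be recruited).

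| e | q | d (points) | share of 6.5 | false-positive rate, n = 750 | n = 975 |
|---|---|---|---|---|---|
| 2% | 40% | 0.2 | 3% | 0.051 | 0.051 |
| 2% | 60% | 0.6 | 10% | 0.058 | 0.061 |
| 5% | 50% | 1.1 | 17% | 0.074 | 0.082 |
| 10% | 40% | 1.2 | 18% | 0.078 | 0.087 |
| 10% | 60% | 3.4 | 52% | 0.300 | 0.373 |
| 5% | 100% (upper bound for this e) | 3.7 | 57% | 0.357 | 0.443 |
| any | 29.4% | 0 | 0% | 0.050 | 0.050 |

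Upper-bound row in full: r = (0.294 − 0.05)/0.95 = 0.2568; d = 0.0372; SE = √(0.2076/750 + 0.1909/712.5) = 0.0233; d/SE = 1.59; rate about 36%.

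**4. Dilution and direction.** If only half the women enter by the verbal-consent route (the site split is not given), removing 2-10% of them makes e 1-5%, and q of 40-60% gives 0.1 to 1.6 points. Removing high-risk women from the caseload arm mimics a benefit; removing them from the standard arm hides one. If instead 2-10% of the standard arm decline and have a 10-20% caesarean rate, that arm's rate rises by 0.2 to 2.2 points, which again favours caseload. Equal, non-selective removal gives no bias.

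**The case against.** The best defence is that the protocol has safeguards. Women with a stated preference are not invited, which should leave fewer disappointed controls; all exclusions will be reported; and an elective caesarean booking is a recordable fact, not an open judgement. Item ii also gives a practical reason: a research midwife cannot attend every home visit. All of this stands, but it reduces or discloses the problem without preventing it. The preference screen acts before allocation and cannot govern refusals or findings of ineligibility afterwards.

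Several stronger readings are tempting, and the documents do not support them.

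- **That Site 1 is equally affected.** Strategies 1 and 3 obtain written consent first. Strategy 2 is ambiguous: item i and the non-enrolment wording fit women who have not yet been randomised.
- **That women are told their arm before signing.** No sentence says so. At Site 2 it is inferred from the home or clinic visit and the lack of blinding.
- **That arm-specific staff rule on eligibility.** The protocol does not say who decides.
- **That allocation concealment fails.** Central telephone randomisation hides the assignment until it is made. The fault is exclusion after randomisation.
- **That a false-positive rate of 36% is to be expected.** It requires every removed woman to be a planned caesarean and all the removals, 5% of a whole arm across both sites, to fall in one arm.

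**Conclusion.** The point holds for Site 2 and needs to be fixed: as written, step 8 removes randomised women under conditions that can differ by arm, against the protocol's own allocation and analysis statements. For Site 1 strategy 2 the finding is only that the passages conflict and must be reconciled.

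Whether bias would arise, how large and in which direction, cannot be determined from the document. The moderate assumptions (2-10% excess removal, 40-60% caesareans among those removed) range from negligible to about half of the design effect. The all-caesarean case is an upper bound for its 5% removal rate, not a forecast. These figures assume no true effect, a two-sided 5% test and a rate of 29.4% in both arms.

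**What to change.** Reconcile Trial Recruitment at both sites with Group Allocation by one of two routes.

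1. **Complete entry before allocation.** Add the consent form to the Site 2 mailing already planned, check every exclusion criterion in the existing telephone call, and contact the randomisation service only once written consent is held.
2. **Treat documented verbal consent as trial consent**, if the ethics committee agrees. Replace the exclusion rule in step 8 so that every randomised woman is analysed in her allocated arm, as far as permission to use her data allows. The documents do not settle that permission for women who refuse to sign.

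Under either route:

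- limit post-randomisation exclusions to ineligibility that already existed before randomisation and is judged blind to arm;
- report them by arm, site and reason;
- delete the statement that equipoise safeguards the randomisation;
- state the order of consent and randomisation for Site 1 strategy 2 explicitly.

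The cost is a change of ethics wording, one more form in an existing mailing and, under the first route, somewhat slower entry.
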